**Methods/design:**

This randomized, open-label clinical trial will randomize 125 HIV-negative Ugandan men requesting voluntary PC to one of five arms (*n* = 25 each). The control group will receive immediate PC, while the four intervention groups will defer PC for 1 month and be provided in the interim with either oral tinidazole, penile topical metronidazole, topical clindamycin, or topical hydrogen peroxide. The impact of these interventions on HIV entry into foreskin-derived CD4^+^ T cells will be quantified ex vivo at the time of PC using a clade A, R5 tropic HIV pseudovirus assay (primary endpoint); secondary endpoints include the impact of antimicrobials on immune parameters and the microbiota of the participant’s penis and of the vagina of their female partner (if applicable), assessed by multiplex enzyme-linked immunosorbent assay and 16S rRNA sequencing.

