### Study treatment groups and randomization

Eligible men (Table 1), who have provided informed, written consent to participate in the trial, will self-randomize, in a computer-generated, open-label fashion to any of the study groups. The study enroller randomly shuffles a pile of sealed, opaque envelopes in the presence of the participant, who then picks a single envelope from the pile. Inside the envelope are details about the participant’s randomization to one of the five study groups (*n* = 25 participants per group), as follows: group 1 is the no treatment (control) group which undergoes immediate PC, as per the normal Entebbe General Hospital protocol; in group 2, participants defer PC for 4 weeks and are provided with tinidazole 2 g by mouth once daily for 2 days (this imidazole class is indicated for treatment of several conditions including amebiasis, giardiasis, trichomoniasis and bacterial vaginosis [17, 18]); in group 3, participants defer PC for 4 weeks and apply topical metronidazole cream 0.75% underneath the foreskin twice daily for 1 week and then twice weekly for the remaining 3 weeks (this topical imidazole is indicated for treatment of bacterial vaginosis [18]); in group 4, participants defer PC for 4 weeks and apply topical clindamycin 2% cream underneath the foreskin twice daily for 1 week and then twice weekly for the remaining 3 weeks (this topical antibiotic is indicated for treatment of bacterial vaginosis [18]); in group 5, participants defer PC for 4 weeks and apply topical hydrogen peroxide 1% gel underneath the foreskin twice daily for 1 week and then twice weekly for the remaining 2 weeks (hydrogen peroxide preparations are indicated for topical treatment of gingivitis/periodontitis [19, 20]). Men in intervention groups 3, 4, and 5 will be reminded about product use twice a week via a telephone call.

**Table 1 Tab1:** Inclusion and exclusion criteria

Inclusion criteria	
Aged ≥18 years	
Male	
Uncircumcised	
HIV-negative	
Willing to give written informed consent	
Willing and able to answer a short social-behavior questionnaire	
Willing to comply with study protocol requirements including randomization and study drug usage	
Available for planned duration of randomization group	
Exclusion criteria	
HIV-infected	
Already circumcised	
Self-reported or physician-noted genital itching/burning, penile discharge, genital ulceration or other possible sexually transmitted infection symptoms	

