### Study follow-up and procedures

Potential study participants will be screened for eligibility (Table 1), confirmed to be generally healthy and without symptomatic genital infections, and then consented by study team clinical staff. Any person with sexually transmitted infection (STI) symptoms at screening, including genital ulceration, urethral discharge or dysuria, will be offered syndromic STI treatment as specified by the Uganda Ministry of Health guidelines and enrolment will be deferred; in addition, any participants found to have asymptomatic gonorrhea or chlamydia upon later polymerase chain reaction (PCR) urine screening will be provided with appropriate treatment. HIV counseling, condom provision, and rapid HIV testing are performed, a social-behavioral baseline questionnaire is administered, and the participant is randomized. Biological samples collected include peripheral venous blood, a first void urine specimen, and genital tract swab samples from the coronal sulcus, inner foreskin, and urethral meatus. All male participants will receive tetanus toxoid vaccination as recommended by the Uganda Ministry of Health guidelines prior to PC. Participants in group 2 have a post-treatment visit on day 3, and those in groups 3–5 on day 8. Men in intervention groups 3, 4, and 5, will be reminded about product use twice a week via a telephone call. After 4 weeks, men are interviewed about product use, tolerability, and sexual practices, provide a repeat blood sample and penile swabs, and undergo routine PC. The excised foreskin tissues are used for immune-based assays to assess the HIV susceptibility of foreskin-derived CD4^+^ T cells (see below). Participants are deemed lost to follow-up if they do not return within 3 days of a scheduled date/visit (see Fig. 1 for visit scheduling).

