**Fig. 1 Fig1:**
[figure not shown]
Schedule of enrolment, interventions, and assessments. *Only applicable for control/nonintervention groups samples. NA = not applicable

At the enrolment visit, female partners who opt to participate and are not actively menstruating will complete a questionnaire regarding genital symptoms and their menstrual cycle; they will self-collect undiluted female genital secretions using a cervicovaginal SoftCup, as well as two vaginal swabs, and provide a first void urine sample for STI testing and 6–8 ml of venous blood. Syndrome-based and PCR-based STI diagnosis and treatment are offered free of charge for all female participants. These study procedures are repeated at the time of her male partner’s PC procedure 4 weeks later.

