### Statistical analysis

The impact of antimicrobial agents on a clade A HIV pseudovirus entry into foreskin-derived CD4^+^ T cells (the primary endpoint) will be assessed by comparing each product group with the untreated control group, using a standard *t* test. The same statistical approach will be used for secondary immune endpoints listed above. The readout for explant HIV infection assays will be the median quantity of HIV p24 antigen produced, and the endpoint will be the percent change in infectivity compared with the vehicle control from the same foreskin, where percentage reduction = ((control − intervention)/control) × 100. A one-sample Wilcoxon-rank test will be used to determine significance (taken as *p* < 0.05). For participants in the intervention groups, the penile bacterial load, microbiota composition, and prepuce cytokine levels will be compared between baseline and on-product visits using a paired *t* test. In female participants, cervico-vaginal bacterial load, microbiota composition, and cytokine levels will be compared between the baseline and follow-up visit using a paired *t* test. In addition, for longitudinally assessed parameters, we will perform an analysis of covariance comparing each intervention group to the control group after adjustment for baseline differences. In case of reported product noncompliance, all participants with missing data will be analyzed according to the group to which they were randomized.

Differences in microbiota biodiversity will be assessed using two biodiversity metrics: diversity (D), calculated as D = Simpson’s diversity index, and evenness (E), calculated as E = D/S, where S is richness. Evenness reflects the dominance by many (i.e., high evenness) versus few (i.e., low evenness) operational taxonomic units (OTUs), whereas richness is a measurement of the total number of unique OTUs present [28]. Differences in overall microbiota composition will be assessed visually based on family-level log-transformed absolute abundance data using nMDS and Bray-Curtis distance; differences are assessed using permutational multivariate analysis of variance (PerMANOVA) based on the log-transformed abundance data [29–31].

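### The baseline-adjusted ANCOVA against control has no control follow-up value for the penile swab parameters, so it cannot separate product effect from change over the 4-week deferral

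*Protocol article*

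**What the plan says.** Under Statistical analysis, the protocol article sets out two analyses of repeated measurements. The first is a paired t test within the product arms: "For participants in the intervention groups, the penile bacterial load, microbiota composition, and prepuce cytokine levels will be compared between baseline and on-product visits". The second is added to it: "for longitudinally assessed parameters, we will perform an analysis of covariance comparing each intervention group to the control group after adjustment for baseline differences".

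The sampling schedule is described elsewhere:

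- Abstract, Methods/design: "The control group will receive immediate PC, while the four intervention groups will defer PC for 1 month".
- Study treatment groups and randomization: "group 1 is the no treatment (control) group which undergoes immediate PC, as per the normal Entebbe General Hospital protocol".
- Study follow-up and procedures, interim visits: "Participants in group 2 have a post-treatment visit on day 3, and those in groups 3–5 on day 8".
- Study follow-up and procedures, final visit: "After 4 weeks, men are interviewed about product use, tolerability, and sexual practices, provide a repeat blood sample and penile swabs, and undergo routine PC".

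For female partners, the text beside Fig. 1 has the enrolment procedures repeated when the man is circumcised, described as his "PC procedure 4 weeks later". It does not say how this applies to couples in which the man is a control.

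**The concern.** An ANCOVA adjusted for baseline needs, in both groups being compared, a baseline value and a later outcome. The control group is there to show what happens over the same interval without product. Here the controls' interval has no length. They are sampled once, before an immediate circumcision, and afterwards no comparable foreskin sample can be taken.

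The protocol thus promises a controlled comparison over time that its described sampling does not provide for penile parameters. Any change during the deferral that has nothing to do with the product would be credited to it, and could mimic or mask a benefit. The protocol's own procedures make such change possible: counselling and condoms at enrolment, and treatment of asymptomatic gonorrhoea or chlamydia found on later PCR. Controls are offered the same, but their only penile sample is taken before any of it could act.

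**Working it through.** **1. Which measurements exist (penile swabs, from the text)**

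| Arm | Enrolment | Day 3 or day 8 | Week 4, at circumcision |
|---|---|---|---|
| Group 1 (control) | yes; circumcised at once | none described | none possible from an intact foreskin |
| Group 2 | yes | day 3 | yes |
| Groups 3–5 | yes | day 8 | yes |

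The paired analysis is itself restricted to the intervention groups, which agrees with this table. The ANCOVA sentence does not.

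**2. What can be estimated**

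Let m be the control mean at enrolment, g the group difference at enrolment, t the 4-week change without product and d the product effect. The available cell means are:

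- control, enrolment: m
- product, enrolment: m + g
- product, week 4: m + g + t + d

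That is three means for four parameters (the design matrix has rank 3 for 4 columns). Only the sum t + d can be estimated. Randomisation justifies g = 0 but does not separate t from d.

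**3. If the model is fitted anyway**

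The protocol gives no figure for this analysis, so there is none to reproduce. The one way to run the model on these data is to enter the control's single value as both baseline x and outcome y. That is an assumption; the document does not say it. Further assumptions: baseline SD 1, no product effect, within-man correlation 0.5, and a common drift t. The 25 per arm is the protocol's.

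- The slope is 1 in controls and 0.5 in the product arm, so the common slope is b = (1 + 0.5)/2 = 0.75.
- The expected group estimate is t, because the arms have equal expected baselines.
- Control residual variance: (1 − 0.75)² = 0.0625.
- Product-arm residual variance: (0.5 − 0.75)² + (1 − 0.5²) = 0.0625 + 0.75 = 0.8125.
- Average: (0.0625 + 0.8125)/2 = 0.4375.
- Standard error: √(0.4375 × 2/25) = √0.035 = 0.187.
- At t = 0.3 SD: 0.3/0.187 = 1.60, and P(Z > 1.96 − 1.60) ≈ 0.36.

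Simulation agrees with this approximation (two-sided 5% level, correlation 0.5):

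| Common drift | False positives, control value used twice | Mean estimate |
|---|---|---|
| 0 | about 5% | 0 |
| 0.25 SD | 26% | 0.25 SD |
| 0.3 SD | 35% | equals the drift |
| 0.5 SD | 73% | 0.50 SD |

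Over correlations of 0.3 to 0.7, the rates are 21–37% at 0.25 SD, 28–51% at 0.3 SD and 62–90% at 0.5 SD. The within-arm paired t test is exposed in the same way: about 30% at 0.3 SD with correlation 0.5.

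**4. Check on the cause**

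When the simulated controls are given their own 4-week value, the mean bias is about 0 and the error rate is 4.6–5.6% for the drifts of 0, 0.25 and 0.5 SD and all three correlations. The missing control follow-up is what produces the error.

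**The case against.** Several counter-arguments have force.

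- **The visit schedule in Fig. 1 is not visible**, and its footnote marks something as applying only to control or non-intervention samples. A later control sample cannot be excluded absolutely. But no text describes one, and immediate circumcision rules out a comparable foreskin sample at 4 weeks.
- **The rates rest on assumptions.** Drift, correlation and the double use of the control value are not in the document, and without drift the error rate is about 5%. This stands: the percentages illustrate sensitivity and do not forecast the trial's error rate. The failure to identify the product effect in step 2 needs none of them.
- **Some sources of drift are weak.** Swabs are frozen and cytokine and microbiota testing needs shipment to Canada, so assay timing need not follow visit timing. Men are not selected on cytokine or microbiota values, so regression to the mean gives no evident arm-level shift. Both points stand; behaviour change and infection treatment remain.
- **The analysis is additional and secondary.** The Discussion treats all outcomes other than tolerability as primarily hypothesis generating, and the 33% go-forward threshold concerns virus entry. This lowers the severity. However, the Discussion's caution is about chance findings from many comparisons, not a systematic shift.

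A reader might also infer that partners of control men have no follow-up. The text does not show that: circumcising the man does not prevent sampling his partner at 4 weeks, and the wording is merely ambiguous. Nor would using the control value twice give controls zero residuals: with common slope b the residual is (1 − b) times the man's deviation from the control mean, a quarter of it at b = 0.75.

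**Conclusion.** The point holds for the penile parameters measured over time. As described, the control group has no outcome separate from its baseline, so the stated ANCOVA cannot distinguish a product effect from any other change over the 4-week deferral. This follows from the described sampling alone. The size of the resulting error depends on drift the document does not quantify: none if there is no drift, and a bias equal to the drift if the control value is used twice.

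It should be fixed, but it does not undermine the trial. A reader might extend it to the primary endpoint. That comparison is an unadjusted t test on tissue taken at circumcision and can be computed as stated; its difference in calendar timing is a separate matter. Nor does the point establish that the female-partner objective lacks a control. The percentages should not be carried over to partners in any case, since their number is not given and they take part only where applicable.

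**What to change.** For the penile bacterial load, microbiota and prepuce cytokine analyses:

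1. Drop the baseline-adjusted ANCOVA against control.
2. Make baseline-adjusted week-4 contrasts among the four deferred arms the randomised longitudinal comparison. These arms share the same interval, so a common drift cancels.
3. Report each product arm at circumcision against control at circumcision as a cross-sectional contrast, stating that it assumes no change over the 4 weeks without product. It carries the same timing difference and does not replace a concurrent control.
4. Label the within-arm paired tests as uncontrolled before-after comparisons.

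For female partners, first reconcile the 4-week repeat sampling with immediate circumcision in control men. If partners of control men are sampled at 4 weeks, keep the ANCOVA for them, because it is then a valid controlled analysis of the second objective. If they are not, make the same changes.

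The cost is analysis wording only, with no new participants, visits or samples. The price is a narrower claim: for penile parameters, controlled longitudinal evidence is limited to differences between products.

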## Hypothesis

Based on these observations, we hypothesize that host immune alterations induced in the uncircumcised penis by gram-negative anaerobic bacteria enhance HIV susceptibility, and that oral and/or topical antimicrobials will reduce foreskin anaerobe load, local tissue inflammation, and therefore lower foreskin susceptibility to HIV.

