### Study outcomes

The broad objectives of this clinical trial are: 1) to quantify the impact of antimicrobial agents on foreskin HIV susceptibility, immunology, and microbiota; and 2) to assess the potential impact of male partner antimicrobial use on the genital immunology and microbiota in their female sexual partner. The primary study endpoint is the percentage HIV pseudovirus entry into foreskin-derived CD4^+^ T cells in the intervention versus control arms, utilizing a validated primary clade A, R5 tropic pseudovirus entry assay [21, 22]. Secondary study endpoints include: 1) foreskin tissue density of HIV-susceptible CD4^+^ T cells; 2) the density and percentage of CD4^+^ T cell subsets (including Th17 cells) in foreskin tissue; 3) the density of Langerhans cells in foreskin tissue based on immunofluorescence microscopy; 4) the presence of foreskin inflammation using cytokine/chemokine quantitation assayed by enzyme-linked immunosorbent assay (ELISA), defined as the presence of ≥ 3/7 inflammatory cytokines within the top quartile for that cytokine; 5) foreskin microbiota composition as characterized using 16S rRNA sequencing; and 6) foreskin tissue explant HIV susceptibility, based on p24 ELISA after ex vivo incubation with a primary HIV isolate.

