### Penile and FGT microbiota characterization

The penile and FGT microbiota will be assessed using barcoded universal primers to amplify V4 hypervariable regions of 16S rRNA genes. Amplicons will be purified, quantified, and pooled prior to sequencing on the Illumina MiSeq platform using the 300 bp paired-end protocol [25]. Sequence read quality will be performed using a standardized bioinformatics pipeline implemented in accordance with the National Institutes of Health Human Microbiome Project standard operating procedures. Operational taxonomic units will be clustered against the Greengenes reference database and taxonomy assigned using –utax through USEARCH, a high-throughput sequence analysis tool that is implemented in QIIME [26] (an open-source microbiome bioinformatics platform). For each sample, vectors of phylotype proportions are clustered into community state types, by computing Jensen-Shannon distances between all pairs of community states and generating a hierarchical clustering using the Jensen-Shannon distance data and Ward linkage [14, 16, 27].

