### Sample size

Based on previously defined pseudovirus entry parameters into inner foreskin-derived CD4^+^ T cells [32], a sample size of 25 participants per group will provide statistical power of 80% to identify clinical approaches that reduce virus entry by ≥ 33% (based on a median virus entry of 15.1% into inner foreskin-derived CD4^+^ T cells), which is the efficacy threshold that we have deemed as sufficient to move a strategy forward.

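### The PerMANOVA labelled as a test of overall microbiota composition uses absolute abundance, so it responds to total bacterial load as well as to the mix of taxa

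*Protocol article*

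**What the plan says.** Secondary endpoint 5 in Study outcomes is "foreskin microbiota composition as characterized using 16S rRNA sequencing". For its overall assessment, Statistical analysis specifies: "Differences in overall microbiota composition will be assessed visually based on family-level log-transformed absolute abundance data using nMDS and Bray-Curtis distance". The formal test follows: "differences are assessed using permutational multivariate analysis of variance (PerMANOVA) based on the log-transformed abundance data". The second clause does not repeat the word absolute, but the natural reading is that the test uses the same data as the ordination. No conversion to proportions is stated for either.

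The same section keeps load and composition apart: "the penile bacterial load, microbiota composition, and prepuce cytokine levels will be compared between baseline and on-product visits using a paired" t test. Hypothesis expects that "oral and/or topical antimicrobials will reduce foreskin anaerobe load". Proportions appear in Penile and FGT microbiota characterization, where "vectors of phylotype proportions are clustered into community state types", but no comparison between groups is stated for those types.

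**The concern.** Composition normally means the relative mix of taxa, and the article's separate listing of load supports that reading. Bray-Curtis distance on log absolute abundance is not a measure of mix alone. If a product lowers every family by the same factor, the mix is unchanged, yet treated samples tend to move away from untreated ones and PerMANOVA can reject. The products are antimicrobials, so a fall in load is an expected effect.

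There is a second consequence. In an unpaired comparison, differences in total load between men enter every distance as noise, which can hide a real change in taxa.

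The Discussion says it is unknown whether and how these agents alter the make-up of the foreskin microbiota. A significant result from this test cannot by itself separate a selective effect on anaerobes from a general fall in load.

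**Working it through.** **Inputs from the article.** 25 men per group (Study treatment groups and randomization); family-level data, log-transformed absolute abundance, Bray-Curtis and PerMANOVA (Statistical analysis). The article gives no figure to reproduce on this point. A 0.05 level is stated beside the explant test and is assumed here.

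**Step 1: one pair of samples.** Bray-Curtis distance is Σ|x_i − y_i| / Σ(x_i + y_i). Let x_i be the log10 abundance of family i, and let every family fall by c log10, so y_i = x_i − c. With F families and mean log abundance m, the distance is Fc / (2Fm − Fc) = c / (2m − c). For illustration, spread a load of 10^6 evenly over 20 families: 50,000 each, m = 4.70.
- c = 0.5: 0.5 / (9.40 − 0.5) = 0.056.
- c = 1.0: 1.0 / (9.40 − 1.0) = 0.119.
- On proportions, the two samples are identical and the distance is 0 for any c.

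So the planned distance changes with load even when the mix does not.

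**Step 2: how often the test rejects for load alone.** Simulation of a two-group PerMANOVA, 25 v 25. None of the following assumptions is in the article.
- Set-up A: 20 families, SD 0.8 log10 per family.
- Set-up B: 20 families with declining mean shares, 20,000 reads per sample, mean load 10^6, SD 1.0 on the natural-log scale per family (1.0 / 2.303 = 0.43 log10), 300 runs, 199 permutations.

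Share of runs significant on the planned scale when every family falls equally:

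| Set-up | Load SD between men (log10) | Fall 0.3 | Fall 0.5 | Fall 1.0 |
|---|---|---|---|---|
| A | 0.3 | – | 99% | 100% |
| A | 0.6 | – | 76% | 100% |
| A | 1.0 | – | 40% | – |
| B | 0.3 | 87% | 100% | 100% |
| B | 0.5 | 49% | 92% | 100% |
| B | 1.0 | 15% | 37% | 95% |

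A dash marks a case not reported. On proportions or log proportions, the same load-only falls are significant in 1–7% (A) and about 4–7% (B) of runs. With 300 runs the standard error at 5% is √(0.05 × 0.95 / 300) = 1.3 points, so these rates agree with the nominal level. With no effect at all, the planned scale rejects in 3–7% of runs (B). The test is valid as a test of any difference; the difficulty is what a rejection means.

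**Step 3: power for a real change in taxa, unpaired.**
- B, five dominant families lowered by 0.5 log10 and shares renormalised, load equal in both groups: planned scale 91%, 32% and 9% at load SD 0.3, 0.5 and 1.0; proportions 99.7–100%.
- B, the same with a 0.3 log10 shift: planned scale 38%, 11% and 9%; proportions 58–62%; log proportions 87–90%.
- 20 families, selective absolute fall of 0.5 log10: planned scale 65%, 19% and 9% at load SD 0.3, 0.6 and 1.0; relative abundance 48%, 53% and 53%.

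The planned scale does better in one of these cases and worse in the others.

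**The case against.** The strongest reply is that absolute abundance is the right scale for this trial. The hypothesis concerns anaerobe load, and the Background ties risk to the density of these bacteria. A product that lowers every family has done something relevant, which an analysis of proportions alone would not show. This stands, and it is why the planned analysis should be kept.

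A second reply is that other planned analyses already separate the two: load is compared on its own, and Simpson diversity and the proportion-based community state types do not change under a uniform fall. This stands in part. Simpson diversity ignores which taxa are present, no test between groups is stated for the state types, and the paired t test and covariance analysis do not say what quantity represents composition. A load result shows that load fell, but not whether the PerMANOVA result reflects load alone.

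Third, relative abundance has its own faults. Proportions sum to one, and power depends on the scale. In set-up A, raw proportions found a 0.5 log10 shift in five families in only 23–25% of runs; in set-up B, raw proportions found a shift of that size in nearly all. This argues for a log scale and for adding an analysis rather than replacing one.

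A reader might also infer that a load-only effect is bound to be declared a composition change, or that the planned scale always loses power. The document supports neither. The first rate ran from 15% to 100% over the falls tried. The second depends on unknown variances and on an unpaired comparison. The PerMANOVA grouping is not stated; if it is within men, stable load differences between them would largely cancel, although a load-only fall on product would still move the samples.

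**Conclusion.** The point holds as a matter of what the test measures. The article fixes an analysis of composition on a scale that also carries total load, while treating load as a separate parameter. A load-only effect can be reported as a composition change: about 40–99% of runs for a uniform 0.5 log10 fall with load SD 0.3 to 1.0 log10 (set-up A), against about 5% on relative abundance. The possible loss of power is real in some settings, but its size cannot be fixed from the document. All percentages rest on assumed family counts, variances and loads; only the dependence on load follows from the formula alone. Severity is low to moderate: the Discussion treats every outcome except tolerability as primarily hypothesis generating, and the stated threshold for moving a strategy forward concerns virus entry.

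**What to change.** 1. Keep the absolute-abundance ordination and PerMANOVA, and label them a joint assessment of load and composition.
2. Add the same ordination and PerMANOVA on log-transformed relative abundance, with the transformation and its constant set in advance.
3. Read both beside the separate comparison of bacterial load.
4. Attribute a change to composition only when the relative-abundance analysis supports it.

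The cost is one extra analysis on data already held, plus a few words in the plan. The drawback is that proportions sum to one: a fall in one family raises the others, so the relative results should be interpreted with the absolute values alongside.
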